### Statistical analyses

#### *Primary analyses*

Data analyses will be performed using the Statistical Analysis System, SAS 9.1.3 (SAS Institute, Inc, Cary, NC, USA). Following intention-to-treat principles, all participants who have been randomized to the two interventions will be included in the analyses. All significance tests will be two-tailed.

#### *Contraceptive initiation (Aim #1)*

Analyses of contraceptive initiation while incarcerated will include the percentage of participants starting a highly effective method requiring infrequent user maintenance (Subdermal implant, injectable contraception, or an IUD) as well as highly effective methods requiring more regular non-coital use (contraceptive pills, vaginal rings, and the patch). Initiation of contraception use (yes/no) will be analyzed using logistic regression to determine if women randomized to the MICA condition are more likely to initiate a contraceptive method while incarcerated than women randomized to the video condition. Baseline randomization characteristics (for example, age, race/ethnicity, and pregnancy intentions) will be incorporated in the initial model to insure randomization was successfully accomplished. Odds ratios and their 95% confidence intervals will be calculated for MICA using the video condition as the referent.

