### Procedures/Interventions

A research assistant (RA) will recruit potential participants in the housing units at the RI DOC. She will identify herself as non-RI DOC staff and inform women that study participation is completely voluntary and will not affect any privileges at the facility. Individuals who are interested in participating will be given an informed consent form to review and the study will be explained. Given that incarcerated populations are vulnerable populations with limited rights, the informed consent process is particularly important. The RA will detail that study participation is not linked to any extra medical or non-medical services in prison and will not influence parole status or any other jail privileges. Additionally, it will be explained that she does not need to participate in the study to receive reproductive health services. It will be explained that this is a confidential study but that if there is any information that a participant may harm herself, another person, or that a child or an elderly or disabled individual is in danger then that information will be reported. If there is a threat made to the security of the prison then prison staff will be informed. Counselors are instructed not to discuss study participation with any one at the RI DOC. All study staff are certified through the hospital in Human Subjects Protection and HIPAA, and a certificate of confidentiality has been obtained to further insure participant confidentiality.

Inclusion and exclusion criteria will be reviewed. If eligible and willing to participate in the study, the informed consent process will be completed (study explained, consent form read to the individual, and questions answered) and forms signed. Locator information will be obtained and consents signed for tracking
[35].

Participants will be randomized by age (25 years or younger *vs*. older than 25 years), race/ethnicity (non-Hispanic White *vs*. other), and pregnancy intentions (wants no more pregnancies *vs*. wants a future pregnancy). Future pregnancy plans will be assessed by a single question: ‘Do you want to have any/anymore children?’ Based on these criteria there will be eight randomization groups. A random number generator will determine intervention status for the eight groups. Intervention status is then placed into sequentially numbered envelopes for the eight groups and each envelope is sealed and opened in order as women become eligible in each of the eight groups.

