### Sample size

The sample size calculation is based on the biological outcomes and is the most conservative estimate. Data from our prior work (project CONNECT
[20]) shows that the 6-month incidence of an STI was 33%
[38]. We assume over a 12-month period this will increase to 43%. From this data, we assume that the intervention will decrease the incidence a moderate amount to 31%. Similarly, we assume a type I error of α = 0.05, an average within-subject correlation of 0.50 and a conservative estimate of a 20% attrition rate
[39]. Using the similar procedure as above, the proposed enrollment of 400 participants (200 participants for each intervention) at baseline will achieve power of 80% to detect assumed differences after considering four repeated measures (3, 6, 9, and 12 months). Our proposed sample size may provide greater power to detect interaction effects, robustness to violations of model assumptions, protection against multiple comparison error rates, and increased efficiency to detect weaker relationships between variables.

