#### *Contraceptive continuation (Aim #2)*

Analyses of contraceptive continuation will include the assessment of highly effective contraception use (yes/no) at the four follow-up time points. In addition to assessment of contraception use, pregnancy intentions will also be assessed at each time point. Generalized linear mixed models (GLMM) will be used to analyze the binary outcome. GLMM allows for flexibility in the distribution of the outcome and can also incorporate repeated measures of both dependent and independent variables. Independent variables in the GLMM will include treatment group, pregnancy intentions, an indicator variable for time as well as risk factors for unplanned/unwanted pregnancy (education, health insurance status, alcohol/drug use, and pregnancy history). Testing the interaction between treatment group and time will inform us whether differences in contraceptive outcomes between treatment conditions become more or less pronounced over the 12-month follow-up.

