#### *Incident STIs (Aim #3)*

Analyses of incident STIs will evaluate all STIs tested throughout the study. GLMM will be used, and we will follow the similar procedure outlined in Aim #2.

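### The stratification factors are not fixed as covariates in the final primary models: Aim 1 enters them only as a check on randomisation, and Aim 2 names neither age nor race/ethnicity

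*Protocol article*

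**What the plan says.** Procedures/Interventions splits women by age (up to 25 or older), race/ethnicity (non-Hispanic White or other) and pregnancy intention, the last taken from one question on whether the woman wants any or more children. "Based on these criteria there will be eight randomization groups", and a random number generator sets the allocation in each. No block size is given.

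The primary analyses then treat these factors as follows.

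- **Aim 1 (logistic regression):** the baseline randomisation characteristics "will be incorporated in the initial model to insure randomization was successfully accomplished". The next sentence announces odds ratios for MICA against video.
- **Aim 2 (GLMM):** the terms named are treatment group, pregnancy intentions, time and risk factors for unplanned pregnancy, given as "education, health insurance status, alcohol/drug use, and pregnancy history". The same section says that pregnancy intentions are assessed at each time point.
- **Aim 3 (GLMM for incident STIs):** "we will follow the similar procedure outlined in Aim #2".

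Age and race/ethnicity come back only as predictors of contraceptive use under Secondary analyses.

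**The concern.** Factors used to restrict the randomisation belong in the primary analysis because the design used them. The article gives a different reason for Aim 1, and that reason fails. A regression of contraceptive initiation on treatment and covariates estimates how the covariates relate to the outcome. It carries no information on whether the envelopes were generated or opened correctly. Calling the model initial also suggests a later one, and the text does not say which of the two gives the reported odds ratio.

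For Aims 2 and 3 the named covariates leave out two of the three stratifiers. The Background reports higher STI incidence in African American and Hispanic women and says that two-thirds of STIs occur below age 25. These are nearly the two cut-points used for stratification, and STI incidence is the outcome on which the trial is sized.

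The pregnancy-intention term in Aim 2 may not be the stratifier. If it is the value measured at each visit, it is post-randomisation, and the MICA sessions discuss pregnancy intentions directly.

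At stake are some precision on the primary outcomes and a primary Aim 1 estimate that is not uniquely defined.

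**Working it through.** **Step 1. Reproduce the stated power.** Inputs from Sample size and Primary analyses: 43% against 31%; "we assume a type I error of α = 0.05"; "All significance tests will be two-tailed"; 200 per arm; 20% attrition; four repeated measures; within-subject correlation 0.50.

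- Completers per arm: 200 × 0.8 = 160.
- Repeated-measures factor: (1 + 3 × 0.5)/4 = 0.625.
- Effective n per arm: 160/0.625 = 256.
- Power = Φ{[|p1 − p2|√n − 1.96√(2p̄(1 − p̄))] / √(p1(1 − p1) + p2(1 − p2))}, with p̄ = 0.37.
- Numerator: 0.12 × 16 − 1.96 × √0.4662 = 1.920 − 1.338 = 0.582. Denominator: √(0.2451 + 0.2139) = 0.6775. Ratio 0.859, so power = **80.5%**.
- In reverse: 253 per arm for a single measurement × 0.625 = 158.1; /0.8 = 197.7, or 198 per arm and 396 in total, against 400 planned.

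The stated 80% therefore follows from an unadjusted comparison. No covariate gain was counted on.

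**Step 2. Effect of leaving out age and race/ethnicity.** The documents give no prognostic strength, so it is assumed: each factor has 50% prevalence and an outcome odds ratio of 1.0, 1.5, 2.0 or 3.0. The marginal risks stay at 43% and 31%. Each scenario has 4,000 simulated trials of 256 per arm, analysed by logistic regression with and without the two factors. Allocation within the eight strata is either in permuted blocks of 4 or simple.

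| OR per factor | Power, blocks: without / with | Power, simple: without / with | Type I error, blocks: without / with |
|---|---|---|---|
| 1.0 | 81.3% / 81.3% | 80.5% / 80.2% | 5.3% / 5.4% |
| 1.5 | 81.5% / 82.0% | 81.0% / 81.1% | 4.8% / 5.1% |
| 2.0 | 80.9% / 82.5% | 80.0% / 81.9% | 4.8% / 5.4% |
| 3.0 | 81.1% / 84.5% | 80.5% / 85.2% | 3.6% / 5.0% |

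Simulation error is about 0.6 points for power, and √(0.05 × 0.95/4000) = 0.34 points for type I error. The gain from adjustment is thus about 0 to 0.5 points at odds ratios of 1.0 to 1.5, 1.5 to 2 at 2.0, and 3 to 5 at 3.0. Under blocking, only the 3.6% at an odds ratio of 3.0 is clearly below 5%.

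**Limits.** One binary outcome at the effective sample size stands in for the GLMM. The other listed covariates are taken not to carry the age and race/ethnicity effects already; if they do in part, the gain is smaller. The article gives no planning rates for Aim 1, so no figure is offered there.

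**The case against.** The strongest reply is that this is a condensed article. The final covariate set is commonly left to an analysis plan, and the text nowhere says that the stratifiers will be removed. Several stronger readings are tempting, and the reply defeats them:

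- *The stratifiers appear only in Aim 1.* Not so: Aim 2 names pregnancy intentions, though perhaps not the baseline value.
- *They will be dropped after a look at the data.* This is inference. No removal rule or p-value criterion is given; the text is silent on whether they stay.
- *Aim 3 copies the Aim 2 covariate list.* The wording is a similar procedure, and the Aim 2 list is labelled as pregnancy risk factors. An STI model with its own risk factors would be consistent with the text.
- *The trial is underpowered as a result.* The 80% reproduces without adjustment. What is forgone is a gain beyond the plan.
- *The type I error is wrong.* Below-nominal error needs blocking within strata, which is not stated, and the deviation is in the safe direction.

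A reader might also want to swap the pregnancy-related covariates in Aim 3 for sexual-risk ones. That is a preference which nothing in the documents settles.

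The reply does not cover what the article does state: a mistaken reason for entering the factors in Aim 1, and a named Aim 2 list that includes several covariates but not two of the three design factors.

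**Conclusion.** The point holds as a modest defect of specification and efficiency. The randomisation-check rationale is wrong, the model behind the Aim 1 odds ratio is left open, and age and race/ethnicity are not named for Aim 2 or, by the reference to a similar procedure, for Aim 3.

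The size depends on prognostic strengths that had to be assumed, and it is small unless age and race/ethnicity are both strong predictors. There is no inflation of type I error and no fault in the sample size. The case for the change rests on coherence with the design and on its negligible cost more than on the power gained.

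**What to change.** State that age group, race/ethnicity and the answer to the baseline stratifying question on wanting children are fixed covariates in the final primary models for Aims 1, 2 and 3, whatever their p-values. Delete the statement that they are entered to check randomisation. In Aim 2, make clear that the baseline pregnancy-intention answer is the adjustment term, and distinguish it from the value measured at follow-up. In Aim 3, name the covariates outright. Add that the resulting odds ratios are conditional on the stratifiers, so that they are not read as marginal ones.

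The cost is analysis wording only. All three variables are known at randomisation, so no new data and no change to the sample size are needed.

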#### *Contraceptive continuation (Aim #2)*

Analyses of contraceptive continuation will include the assessment of highly effective contraception use (yes/no) at the four follow-up time points. In addition to assessment of contraception use, pregnancy intentions will also be assessed at each time point. Generalized linear mixed models (GLMM) will be used to analyze the binary outcome. GLMM allows for flexibility in the distribution of the outcome and can also incorporate repeated measures of both dependent and independent variables. Independent variables in the GLMM will include treatment group, pregnancy intentions, an indicator variable for time as well as risk factors for unplanned/unwanted pregnancy (education, health insurance status, alcohol/drug use, and pregnancy history). Testing the interaction between treatment group and time will inform us whether differences in contraceptive outcomes between treatment conditions become more or less pronounced over the 12-month follow-up.

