### Motivational Interviewing (MI) to decrease unplanned pregnancies and STIs

MI provides an empirically supported style for matching counseling to an individual’s readiness to change. Based on the principles of motivational psychology, client-centered therapy, and the Transtheoretical Model (TTM),
[18,19] MI represents a general and practical approach for facilitating behavior change by enhancing and eliciting a client’s own internal motivation for change.
[20] Responsibility for changing a behavior is assumed to lie within the individual, and ambivalence is recognized as a natural part of this change process. MI is designed to assist clients in working through ambivalence and in moving toward change. Their ambivalence may reflect a desire for a pregnancy in which case the MI counselor changes focus to having a healthy pregnancy. Utilizing MI techniques, the counselor helps the participant identify barriers to using birth control and methods for overcoming those barriers. MI targets increasing interest and confidence in accessing and using condoms and other forms of birth control and use of family planning professionals. Elements of the protocol are tailored to a woman’s specific needs including holding off on pregnancy until she is ready (for example, is financially stable or has a steady partner); it focuses on good and not-so-good ways regarding how to effectively negotiate use of contraceptives with partners (not so good would be to carry a knife to dissuade aggressive partners), decreasing use of alcohol and other drugs during sex (which may make it harder to use birth control and condoms), increasing use of referrals to family planning clinics, and identifying barriers specific to women and generating possible solutions. The MI counselor utilizes techniques including providing personalized feedback, reflective listening, exploring pros and cons of change, giving affirmations, supporting client autonomy and self-efficacy, eliciting ‘self-motivational statements’ (problem recognition, intention to change, optimism about change), and generating solutions to potential barriers to change. Of critical importance, MI emphasizes client’s personal choice regarding change, de-emphasizes labeling the client and her behaviors, and avoids arguing with or confronting the client with the need to change.

Published studies include successful MI interventions with individuals who smoke tobacco
[21], those who are addicted to heroin on methadone

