Before the first intervention session, a 45-60-minute computer-assisted questionnaire will be administered to the participant. From the baseline questionnaire, we will gather the following information: demographics, obstetric and gynecologic history, length of stay in prison, medical insurance, primary care provider or clinic, relationship violence, childhood abuse, addiction, and depression. These measures will aid in assessing the complex context in which a woman ‘chooses’ to initiate or not initiate contraceptive services.

The counselor/RA will then administer MICA or video according to randomization. Self-obtained vaginal samples for *Trichomoniasis vaginalis *, *C. trachomatis*, and *N. gonorrhoeae* will be obtained as well as a urine sample for a pregnancy test. Contraceptive, sexual, and drug-related risk behaviors will be measured via a calendar recall behavioral assessment, a Timeline Followback (TLFB) calendar of the prior 90 days at baseline and at each follow-up visit
[36,37]. This assessment utilizes a calendar-based recall method using anchor dates to facilitate a more accurate response set. It also allows for a more thorough assessment of risk behaviors by allowing for the analysis of risk patterns by sexual partner, drug, and alcohol use and the co-occurrence of sexual- and drug-related risk, all within the context of life events. A detailed assessment of sexual behaviors and condom use with each of the participant’s other sex partners will be made by the participant.

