#### *MICA*

Participants randomized to MICA will receive all core MI elements in the MICA sessions. A key component of any MI-based intervention is for the counselor to support autonomy by explicitly stating that it is the participant, not the counselor, who will make decisions regarding behavior change. Counselors will lead the participant in a directed, empathic discussion that includes a review of the Timeline Followback (TLFB) calendar, pregnancy intentions, the pregnancy and STI risk assessment printouts, and Stages of Readiness to Change. The behaviors targeted vary depending on the needs of the participant with the overall goal of decreasing the risk for unplanned pregnancies and STIs. For example, some want to focus on decreasing the number of sex partners, some using birth control consistently, and others want to see a medical provider to initiate a birth control method. The counselor will support the participant’s decision to make, or consider the possibility of, change. All MICA participants will receive: (1) feedback on personal risks for pregnancy and STIs; (2) clear advice to avoid pregnancy (until it is desired) and STIs that might impact future fertility by either using highly effective contraceptives and condoms consistently and correctly or staying abstinent; and (3) a review of the menu of options by which to prevent pregnancy and STIs. Detailed education about contraceptive choices is offered according to the participant’s needs and requests. The session will end with the development of a ‘CARE plan’ in which the participant lists her goals and methods for reaching her STI and pregnancy prevention goals. A second MICA session will be conducted 3 months after release and include a review of the’CARE plan’ as well as elements provided in session one. If a woman chooses no method or decides she wants to become pregnant then preconception counseling is offered.

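### As naturally read, the primary Aim 2 model adjusts the MICA effect for pregnancy intentions re-measured after randomisation, so its treatment coefficient may not be the total effect of assignment

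*Protocol article*

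**What the plan says.** The Aim 2 section stands under Primary analyses in the protocol article. Highly effective contraceptive use (yes/no) at 3, 6, 9 and 12 months is analysed by a generalized linear mixed model (GLMM). Three statements in that section bear on the covariates:

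- On measurement: "pregnancy intentions will also be assessed at each time point".
- On the choice of model: a GLMM "can also incorporate repeated measures of both dependent and independent variables".
- On the model terms: "Independent variables in the GLMM will include treatment group, pregnancy intentions, an indicator variable for time as well as risk factors for unplanned/unwanted pregnancy". The risk factors are given as "education, health insurance status, alcohol/drug use, and pregnancy history".

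The Aim 1 section differs. It labels its adjustment variables as baseline randomization characteristics and names age, race/ethnicity and pregnancy intentions as examples.

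On the intervention, the MICA section says that counselors lead a discussion that includes "a review of the Timeline Followback (TLFB) calendar, pregnancy intentions" and other items. The Background section on motivational interviewing (MI) describes tailoring that includes postponing pregnancy until the woman is ready, and "decreasing use of alcohol and other drugs during sex".

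For incident STIs (Aim 3), the article says "we will follow the similar procedure outlined in Aim #2". The secondary TLFB analysis uses the same formula of words.

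**The concern.** Pregnancy intentions at follow-up are measured after randomisation. The first MICA session precedes all four follow-ups, and the second, at 3 months after release, precedes the 6-, 9- and 12-month ones. If MICA leads more women to want to postpone pregnancy, and such women use contraception more, then part of the effect runs through intentions.

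A model that holds follow-up intentions fixed removes that part. It can also create an association that randomisation had excluded. Women with the same follow-up intention in the two arms need no longer be alike in unmeasured causes of both intention and use, such as general motivation or partner circumstances.

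The treatment coefficient would then answer a narrower question than whether assignment to MICA raises continued use. No Aim 2 model without this covariate is described.

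**Working it through.** **1. Which measurement enters the model?** Four features of the text favour follow-up values for pregnancy intentions:

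- The sentence on measurement at each time point comes shortly before the covariate list.
- The sentence on repeated independent variables stands between the two.
- The word baseline, used for Aim 1, is absent for Aim 2.
- Age and race/ethnicity, the other two stratification factors, are not in the Aim 2 list, so the term does not read as the randomisation stratum.

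For alcohol/drug use the text does not say. Drug-related behaviour is recorded on "a Timeline Followback (TLFB) calendar of the prior 90 days at baseline and at each follow-up visit", so follow-up values exist, but nothing states that they are the ones entered. The same silence covers health insurance.

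**2. The plan's own figure.** The sample size is not at issue, and it reproduces. Inputs from the Sample size section: 43% v 31%, two-sided α = 0.05, power 80%, four measures with correlation 0.50, attrition 20%.

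- Per arm, one measure: [1.96·√(2·0.37·0.63) + 0.8416·√(0.43·0.57 + 0.31·0.69)]² / 0.12² = 253.
- Repeated-measures factor: (1 + 3·0.5)/4 = 0.625, and 253 × 0.625 = 158.1.
- Attrition: 158.1/0.80 = 198 per arm (199 if rounded up at each step), so 396 to 398 in total against 400 stated.

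**3. Size of the distortion.** The documents give no effect of MICA on intentions and none of intentions on use, so all inputs here are assumptions. The models are for one visit and ignore the repeated measures.

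*Small-shift case, by hand, no shared unmeasured cause.* Let e(x) = 1/(1 + exp(−x)). Assume P(wants to avoid pregnancy) = e(1 + 0.2·MICA) and P(use) = e(−1 + 0.3·MICA + 1.5·intention).

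- Video: intention e(1) = 0.731. Use = 0.269·0.269 + 0.731·0.622 = 0.527, odds 1.116.
- MICA: intention e(1.2) = 0.769. Use = 0.231·0.332 + 0.769·0.690 = 0.607, odds 1.545.
- Total odds ratio (OR) = 1.545/1.116 = 1.38. Adjusted for intention, OR = exp(0.3) = 1.35.

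*Larger range, by simulation (200,000 women per scenario; second decimals carry simulation error).* P(baseline intention) = e(0.5 + c·U); P(follow-up intention) = e(−0.3 + 1.0·baseline intention + a·MICA + c·U); P(use) = e(−1 + d·MICA + b·follow-up intention + c·U). U is an unmeasured standard normal cause.

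| a | b | c | d | OR, baseline intention only | OR, follow-up intention added |
|---|---|---|---|---|---|
| 0 | 1.0 | 0.5 | 0.4 | 1.40 | 1.44 |
| 0.25 | 1.0 | 0.5 | 0.4 | 1.51 | 1.45 |
| 0.75 | 1.0 | 0.5 | 0.4 | 1.63 | 1.41 |
| 0.75 | 1.5 | 0.5 | 0.4 | 1.73 | 1.42 |
| 0.5 | 1.0 | 0.5 | 0 | 1.09 | 0.97 |
| 0.75 | 1.0 | 0.5 | 0 | 1.15 | 0.97 |
| 0.5 | 0 | 0.8 | 0 | 0.99 | 0.95 |
| 0.75 | 0 | 0.8 | 0 | 1.00 | 0.94 |

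Row 1: if MICA does not move intentions there is no attenuation. The small rise is non-collapsibility of the odds ratio. Rows 2 to 4: the mediated part is lost. Rows 5 and 6: a fully mediated effect disappears. Rows 7 and 8: a true null moves slightly below 1, through U alone.

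**The case against.** The strongest reply is that the article does not pin the term down. Pregnancy intention is also a baseline stratification factor, the sentence on repeated independent variables describes what a GLMM can do, and a journal article may leave the exact measurement to a fuller document. It is true that the model sentence itself does not say follow-up values. But the surrounding sentences point that way, and a reader who followed the article would fit the time-varying term. This is a model statement that misleads as it stands, which is more than a missing detail.

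A second reply is that MICA need not shift intentions. The article stresses that the participant decides, provides preconception counseling for women who come to want a pregnancy, and enrols only women who say they plan none within 12 months. This stands: the distortion is conditional, and the direction of any shift is not established. Because the intervention works on exactly this topic, however, the primary analysis should not depend on there being no shift.

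Several stronger readings are tempting, and the document does not support them:

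- *That alcohol/drug use is certainly adjusted for at follow-up values.* This is an inference from repeated collection. The Background names use during sex, which is narrower than the covariate, and the MICA section does not list substance use among its examples of targeted behaviours.
- *That Aim 3 and the TLFB analysis inherit the same covariates.* They are tied to Aim 2 only by a similar procedure.
- *That the intention-to-treat statement is broken.* It promises that all randomized women are included, and covariate choice does not change that. What changes is the effect being estimated.
- *That the sign will reverse.* With no direct effect and no shared unmeasured cause, the adjusted OR is exactly 1.00. Falling below 1 needs a shared cause of assumed strength.

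**Conclusion.** The point holds for pregnancy intentions in the primary Aim 2 model, on the natural reading of the text. If MICA shifts follow-up intentions, the treatment coefficient is not the total effect of assignment. Attenuation is the likely direction if MICA strengthens the wish to postpone pregnancy and that wish raises use. Some bias from shared unmeasured causes is possible as well.

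Size and sign cannot be fixed from the document. Under the assumed inputs, the odds ratio changes from 1.38 to 1.35 at the small end and from 1.63 to 1.41 in a material case, and a fully mediated effect disappears. If MICA leaves intentions unchanged there is no attenuation.

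For alcohol/drug use, health insurance, Aim 3 and the TLFB analysis the concern is conditional on choices that the text does not state. Because the safe specification costs almost nothing, the model should be corrected whichever of these sizes is nearer the truth.

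**What to change.** State that the primary Aim 2 model contains treatment, time, treatment-by-time and baseline covariates only: baseline pregnancy intentions and the other two stratification factors (age and race/ethnicity), plus baseline education, health insurance, alcohol/drug use and pregnancy history. State that the Aim 3 and TLFB models follow the same rule.

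Move follow-up pregnancy intentions and substance use to a secondary or mediation analysis, labelled as such. The section on predictors of contraceptive use already plans to study processes of change, so it fits there.

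The cost is a sentence or two in the analysis section. The baseline values are already to be collected, and neither the sample size nor the visit schedule changes.
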